### Longitudinal analysis

Mixed models will be used for the majority of the longitudinal analyses to estimate the trajectory of HRQoL over time. Correlation between repeated measures within centres and participant will be accounted for. Differences between groups at different time points will be assessed using adjusted means. Assuming a design effect of 2 for the quality of life instruments in the target population and a correlation of 0.65 between a participant’s repeated measurements, the study would be powered at 80% to detect changes as small as 0.45 standard deviations per six-month period within a group containing 38 patients.

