## Methods/Design

### Study design

The study uses an “accelerated longitudinal design”, comprised of cross-sectional and longitudinal components. The cross-sectional data are collected at the baseline interview and from clinical records in Year 1. The longitudinal data are collected from interviews 2 and 3 (12 and 24-months after the initial interview) and from clinical records in Years 2 and 3. This study design is optimal since it: 1) allows for the provision of timely results from an initial cross sectional analysis, and 2) by including the prevalent dialysis patients at baseline and the incident patients eligible for dialysis each year, it also allows for sufficiently powered longitudinal analyses, without the need for extended recruitment that would be necessary if the study used a dialysis inception cohort.

The nephrology teams responsible for their medical care have undertaken the identification of potential participants. All eligible (and consenting) participants will be contacted by telephone to arrange an interview. Data will be collected at each of the three interviews using structured questionnaires administered to participants by trained interviewers and from clinical records by the research nurses. The first Baseline Interview will be administered to all eligible participants already on dialysis for at least 90 days at the start of the study and to all new patients who are eligible for dialysis each year. Follow-up questionnaires are then administered to survivors 12 and 24-months later. The questionnaires have been piloted with 60 older patients with CKD and found to be acceptable and to cover questions and issues of greatest relevance to them [8]. Each interview will be designed to take 45-60 minutes and will be conducted either on the telephone or face to face depending on patient preference.

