### Data analysis

All analyses will be performed using Stata 11.0 (or subsequent versions). Confidence intervals will be provided in all cases. All data will be described using appropriate summary statistics and frequency tables where necessary. Associations between the variables will be assessed in terms of statistical significance at a level of P <0.05.

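### The longitudinal power figure (0.45 SD per six months, 38 patients) does not fit the yearly interviews and does not follow from its stated inputs

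*Protocol article*

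**What the plan says.** The Longitudinal analysis section plans mixed models for the course of quality of life and then gives one power statement. Its premises are: "Assuming a design effect of 2 for the quality of life instruments in the target population and a correlation of 0.65" between repeated measurements on the same participant. Its conclusion is 80% power to "detect changes as small as 0.45 standard deviations per six-month period within a group containing 38 patients".

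The Data analysis section sets the significance level: "Associations between the variables will be assessed in terms of statistical significance at a level of P <0.05". It does not say whether tests are one- or two-sided.

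The Study design section fixes when quality of life is measured. After the baseline interview, the longitudinal data come from "interviews 2 and 3 (12 and 24-months after the initial interview". The Abstract likewise describes the interviews as yearly. No six-month quality-of-life measurement appears anywhere in the article.

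**The concern.** Two things do not fit. The time unit of the detectable change is half the shortest interval between interviews, so no six-month change is directly observed. And the group size, design effect, correlation, power and significance level together determine a detectable change for a simple two-interview comparison, which is not 0.45 SD.

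This is the article's only power statement for quality-of-life change over time, and the Study design section justifies the mixed prevalent and incident cohort partly by the power of its longitudinal analyses. A reader who takes 0.45 SD at face value could treat a flat trajectory in a subgroup of about 38 as adequately powered evidence of no change. The reader also cannot tell what yearly change or slope such a subgroup could show.

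**Working it through.** **Inputs**
- Group size 38, design effect 2, correlation ρ = 0.65, power 80%, target 0.45 SD: Longitudinal analysis section.
- Significance level 0.05: Data analysis section. Two-sided is my assumption; one-sided is tried below.
- Interviews at 0, 12 and 24 months: Study design section.
- Multiplier: z(0.975) + z(0.80) = 1.960 + 0.842 = 2.802.

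**Step 1. Try to reproduce 0.45 as a change between two interviews**
- SD of a change = √(2(1 − ρ)) = √(2 × 0.35) = √0.70 = 0.837 SD.
- Effective sample size = 38 / 2 = 19.
- Detectable change = 2.802 × 0.837 / √19 = **0.538 SD** (normal). With the noncentral t on 18 df it is **0.569 SD**.

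The stated 0.45 is not reproduced, and the interval to which 0.54–0.57 applies is 12 months.

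**Step 2. Power at 0.45 SD with 38 patients**
- Standard error = √(0.70 / 19) = 0.192, and 0.45 / 0.192 = 2.344.
- Power = Φ(2.344 − 1.960) = **65%** (normal); **60%** (t).

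**Step 3. Patients needed for 80% power at 0.45 SD**
- n = 2 × 0.70 × (2.802 / 0.45)² = 54.3, so **55** (normal). With the t distribution, about **59**.

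**Step 4. Read 0.45 as a linear rate instead**
- Times 0, 1 and 2 years give Sxx = 2. Under compound symmetry the slope variance per person is (1 − ρ) / Sxx = 0.35 / 2 = 0.175 per year².
- Detectable slope = 2.802 × √(0.175 / 19) = **0.269 SD per year** (t: 0.284), or 0.134 SD per six months.
- Taken literally as a rate, 0.45 SD per six months is 0.9 SD between consecutive interviews and 1.8 SD over 24 months, far above what is detectable.

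**Step 5. Other readings of the inputs (detectable change, n = 38, normal approximation, two-sided unless noted)**

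| Variant | Detectable change (SD) |
|---|---|
| Paired change, one-sided | 0.477 |
| Paired change, design effect ignored | 0.380 |
| Variance 1 − ρ² (baseline-adjusted) | 0.488 |
| Mean of the two follow-ups minus baseline | 0.466 |
| Design effect and correlation both ignored | 0.4545 |
| Variance 1 − ρ², one-sided, t | 0.451 |
| Mean of three follow-ups minus baseline | 0.439 |
| Mean of four follow-ups minus baseline, t | 0.450 |
| Variance 0.70 used as if it were the SD | 0.4499 |

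The variants that land on or close to 0.45 each discard stated inputs, use a one-sided baseline-adjusted test that is not a test of mean change within one group, assume more than the two follow-ups that exist, or omit a square root. A design effect of about 1.4 in place of 2 would also give 0.45.

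**Step 6. Is halving the sample the right use of the design effect?**
The Cross sectional analysis section states 0.55 SD for 106 per group and 0.8 SD for 53 per group. Dividing n by 2 gives 2.802 × √(2/53) = 0.544 and 2.802 × √(2/26.5) = 0.770, near the stated values. Without the division they would be 0.385 and 0.544. So halving matches the plan's apparent convention, but this is a back-calculation: that section names no design effect.

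**The case against.** The strongest reply is that the article gives no formula. It names no test, no sidedness and no number of measurements behind the figure, and it plans mixed models, not a two-interview comparison. If the calculation was made for six-monthly interviews, one superseded schedule could explain both the unit and the value: four follow-ups averaged against baseline give 0.450 with the t distribution. The design effect is also attached to the quality-of-life instruments, and centre effects may largely cancel in a within-person change. Without it the detectable change is 0.38 SD (0.39 with t), and power at 0.45 is about 90%. Finally, a slope from yearly data can legitimately be expressed per six months, and on that reading the study has more than enough power at 0.45.

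Part of this stands. The origin of 0.45 cannot be known. A reader might infer that the design effect was entered wrongly, or that a square root was dropped; the second matches exactly, but several routes reach the same number, so the article supports no particular diagnosis. A reader might also infer that the longitudinal analyses are simply underpowered. The documents do not support that either, because as a rate the claim is conservative.

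What does not stand is the figure itself. The design effect is a stated premise of the sentence, so dropping it is not a reading of that sentence. A schedule with four follow-ups is not this study's schedule. And a rate per six months computed on the real schedule is 0.13, not 0.45.

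**Conclusion.** Wrong as written; should-fix. The six-month unit does not match yearly interviews, and the value does not follow from the stated inputs under any standard two-sided 5% calculation on the actual schedule. As a change between two interviews it is optimistic: 0.54–0.57 SD is detectable, and power at 0.45 is 60–65% instead of 80%. As a linear rate it is conservative: about 0.27 SD per year is detectable.

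These results assume a two-sided test, a design effect that halves the sample, and 38 participants contributing every interview used. The slope also assumes compound symmetry and no attrition. The Survival analysis section expects high mortality, and if 38 is a baseline count, deaths would reduce power below these values; that was not modelled.

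It would go too far to call this a flaw in the study's size. Expected enrolment is derived from registry counts and a 70% recruitment rate in the Study participants section, and nothing shows that it rests on this figure. Nor does the figure, original or corrected, power the hypothesis that trajectories differ between patient groups, since it concerns change within one group.

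**What to change.** In the Longitudinal analysis section:
- Delete the reference to a six-month period.
- Either restate the detectable within-group change as about 0.54–0.57 SD between two consecutive annual interviews, with 38 patients contributing both (80% power, two-sided 5%, design effect 2, correlation 0.65); or give a detectable slope of about 0.27 SD per year (0.28 with t), stating that it assumes compound symmetry and three completed interviews for all 38.
- Name the test and its sidedness, and say how the design effect enters. If the authors used another method, they should state it and recompute on the 0/12/24-month schedule.
- Say whether 38 is the number at baseline or the number still interviewed at follow-up.

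The cost is wording and a short recalculation. Eligibility, interview schedule, outcomes and analysis method are unchanged.

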### Survival analysis

With the high mortality rate, 24 months of follow up of this cohort will have sufficient power to determine impact on survival. It will identify which key HRQoL measures provide the best discrimination and calibration in determining outcome, so that an abbreviated assessment can potentially be incorporated into evidence-based guidelines to clinical practice. The survival analysis will be performed initially using Cox’s proportional hazards regression which has the potential to detect a hazard ratio of 0.8 with 80% power, and p <0.05 will be considered significant.

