### Study participants

Our cohort will consist of dialysis and pre-dialysis patients recruited from three services across New Zealand, each serving different patient populations using contrasting models of care for dialysis delivery. These are: Middlemore Hospital (Counties Manukau District Health Board (DHB)), the largest dialysis service in New Zealand, providing both home and facility-based dialysis in mostly urban settings including a large proportion of New Zealand Māori and Pacific population; Dunedin Hospital (Southern DHB), a medium sized dialysis service providing entirely home-based dialysis in mixed urban and rural settings; and Hastings Hospital (Hawkes Bay DHB), a small sized dialysis service providing both home and facility-based dialysis in mostly rural settings. There is always a tension between the number of sites and speed of recruitment and the desire to carefully manage recruitment and the study process. By recruiting from three sites we ensure a range of participant characteristics in the study that are representative of New Zealand, while also ensuring that the study is efficient in terms of project management and data analysis. Using registry data from the Australian & New Zealand Dialysis and Transplant registry (ANZDATA), and a recruitment rate of 70%, it is estimated that we will enroll 160 to 172 prevelant participants and approximately 40 incident participants in the first year (Figure 1).

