### Cross sectional analysis from baseline data

Linear mixed models will be used to model quality of life measures (accounting for clustering within centres) based on subject demographics (including age, sex, ethnicity, socioeconomic status), co-morbidities, and modality and duration of dialysis. The prevalent dialysis participants will be grouped for analysis according to their vintage on dialysis, and combined for analysis with the incident patients in Year 1. Differences between categorical measures (e.g., ethnicity) will be assessed using adjusted means. Relationships between continuous measures (e.g., quality of life and dialysis duration) will be assessed using correlations. The study is powered at 80% to detect differences between means of 0.55 standard deviations for two groups sized 106 patients each (half of the sample), and differences of 0.8 standard deviations between two groups sized 53 patients each (quarter of the sample). These detectable differences are considered to be of clinical importance.

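### The survival section's 80% power for a hazard ratio of 0.8 is unattainable for any two-group comparison, and no stated mortality or cohort size supports it per SD of HRQoL

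*Protocol article*

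**What the plan says.** The Survival analysis section opens with a general assurance: "With the high mortality rate, 24 months of follow up of this cohort will have sufficient power to determine impact on survival". It then says the aim is to find which HRQoL measures best predict outcome, and closes with the specific claim that the analysis will use "proportional hazards regression which has the potential to detect a hazard ratio of 0.8 with 80% power", adding that "p <0.05 will be considered significant". It gives no number of deaths, mortality rate, group split or covariate scale, and does not say whether the test is one- or two-sided.

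Cohort size appears elsewhere. The Study participants section estimates that "we will enroll 160 to 172 prevelant participants and approximately 40 incident participants in the first year", which makes 200 to 212. The cross-sectional section uses "two groups sized 106 patients each (half of the sample", again 212. The Study design section says new eligible patients are also interviewed each year, so the final cohort may be larger, but the text gives no later numbers and Figure 1 is not shown.

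Two kinds of survival question are planned. The Hypotheses section expects HRQoL to be positively associated with survival. Aim 2 compares survival by dialysis modality, by location, and against conservative care.

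**The concern.** The power of a Cox model depends on the number of deaths and on the spread of the covariate, not on the number enrolled. A hazard ratio of 0.8 is a modest effect, and between two groups it normally takes several hundred deaths to detect. A cohort of a little over 200 is visibly too small for that.

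What is at stake is how a null survival result is read. The Discussion anticipates that conservative management might prove to have outcomes similar to dialysis, and that this would then shape what patients are told. Aim 3 is to develop guidelines. If a study described as having 80% power for a hazard ratio of 0.8 finds no significant difference by modality, location or conservative care, readers will tend to take that as similarity. With the power actually available, such a result would be the likely one even if a difference of that size existed.

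**Working it through.** **Inputs from the article.** Hazard ratio 0.8, power 80%, significance level 0.05, follow-up 24 months; 200 to 212 participants in the first year.

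**Assumptions.** Two-sided testing, with one-sided results also shown. For the final cohort, two further intakes of 40, giving 280 to 292. For mortality, a range of 30% to 75% at 24 months, with 100% as the upper bound.

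**Deaths required (Schoenfeld).** (1.960 + 0.842)² = 7.849 and (ln 0.8)² = 0.0498.

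- Per SD of a continuous covariate: D = 7.849 / 0.0498 = 157.6, so 158.
- Two groups with share p: D = 7.849 / [p(1 − p) × 0.0498].
  - 50:50: 157.6 / 0.25 = 630.5, so 631 (Freedman's formula gives 636).
  - 25:75: 157.6 / 0.1875 = 840.7, so 841.
  - 20:80: 157.6 / 0.16 = 985.2; from unrounded terms, 986 after rounding up.
- One-sided: 497 for equal groups, 125 per SD.

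The 20:80 split bears on conservative care. Prevalent participants are on dialysis by definition, so in the first-year cohort the conservative group can be at most the 40 or so incident patients: 40/200 = 20% or 40/212 = 19%. The Inclusion criteria say only a proportion of them will decline dialysis.

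**Can the stated 80% be reproduced?** Power for two equal groups is Φ(√(D/4) × 0.223 − 1.960).

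- All 212 die: √53 × 0.223 = 1.62; Φ(−0.34) = 37%.
- All of an assumed 292 die: √73 × 0.223 = 1.91; Φ(−0.05) = 48%.
- One-sided, the same two cases give 49% and 60%.

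No two-group version reaches 80%, and this needs no mortality assumption, because 100% mortality already falls short.

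Per SD, power is Φ(√D × 0.223 − 1.960), which reaches 80% at 158 deaths. As a share of the cohort:

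- 158/212 = 75% and 158/200 = 79%.
- 158/292 = 54% and 158/280 = 56%.

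**Power at HR 0.8 and detectable HR, 212 participants, two-sided.** Detectable HR at 80% power is exp(−2.80/√D) per SD and exp(−5.60/√D) for equal groups.

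| Assumed 24-month mortality | Deaths | Power, equal groups | Power, per SD | Detectable HR, equal groups | Detectable HR, per SD |
|---|---|---|---|---|---|
| 30% | 64 | 14% | 43% | 0.50 | 0.70 |
| 40% | 85 | 18% | 54% | 0.54 | 0.74 |
| 50% | 106 | 21% | 63% | 0.58 | 0.76 |
| 63% | 134 | 25% | 73% | 0.62 | 0.79 |
| 100% | 212 | 37% | 90% | 0.68 | 0.82 |

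The 63% row comes from the only usable survival figure in the article, the mean of 2 years quoted in the Background for an external dialysis group. That wording is ambiguous. Read as an exponential mean, it implies 1 − e⁻¹ = 63% dead at 24 months. At the same mortality, an assumed 292 participants would give 185 deaths and 86% power per SD.

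**The case against.** The strongest reply is that the sentence concerns HRQoL, not groups. The text just before it is about HRQoL measures as predictors, and the survival hypothesis is about HRQoL. The section never attaches 0.8 to modality, location or conservative care. On this reading the claim might even be true. If 0.8 referred to a change of 0.55 SD, a size the cross-sectional section treats as clinically important, it would need 7.849 × 0.55² / 0.0498 = about 48 deaths, fewer than any row of the table. This stands in part: the claim is not impossible for HRQoL. But the article states no such unit, and survival by group is an explicit part of Aim 2 with no other power statement to cover it.

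Second, 212 is only the first-year figure and later intakes may raise it. That also stands, and is why the larger assumed cohort is shown throughout. It helps the per-SD reading materially and does not rescue the two-group reading.

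Third, the wording is hedged, the study is observational, no sample size depends on 0.8, and the Data analysis section promises confidence intervals in all cases. These points lessen the harm, but a specific printed figure that the design lacks for its group comparisons still misleads. Nor is this merely detail left to a fuller plan: no further document can produce 631 deaths among 212 or 292 people.

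Three stronger readings are tempting and should not be drawn:

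- A reader might infer that the cohort cannot supply the 158 deaths needed per SD. It can, if mortality is high enough.
- A reader might double the required deaths using the design effect of 2 in the Longitudinal analysis section. That figure is stated for the quality of life instruments, not for time to death.
- A reader might insert a familiar dialysis mortality rate as the expected one. The article gives none, so any rate is an assumption.

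**Conclusion.** For every two-group survival comparison in Aim 2, 80% power at a hazard ratio of 0.8 is arithmetically out of reach. The most favourable split needs 631 deaths, about three times first-year enrolment, and power is at most 37% with 212 participants or 48% with an assumed 292, even if everyone died. This rests only on the stated 0.05 level taken as two-sided; one-sided testing changes the size of the shortfall, not the conclusion.

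For a continuous HRQoL score the claim is unsupported rather than wrong. Per SD it requires about 75% to 79% mortality at 24 months in the first-year cohort, or 54% to 56% in the assumed larger one. The article describes mortality only as high, and gives neither a rate nor a final cohort size. Its assurance that "24 months of follow up of this cohort will have sufficient power to determine impact on survival" therefore cannot stand as a general statement.

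**What to change.** Restate the power sentence so that it gives:

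- the unit or contrast to which the hazard ratio refers;
- the final cohort size, including intakes after the first year;
- the sponsor's own expected number of deaths D, for example from mortality in the registry already used for the recruitment estimate;
- the hazard ratio detectable with 80% power, separately per SD of HRQoL, exp(−2.80/√D), and between two equal groups, exp(−5.60/√D), with a note that unequal groups do worse.

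As an illustration only, 64 to 134 deaths (30% to 63% of 212, assumed) would give about 0.70 to 0.79 per SD and about 0.50 to 0.62 between equal groups.

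Remove the claim of sufficient power at 0.8 for group contrasts. Say that a non-significant survival difference by modality, location or conservative care will be interpreted from its confidence interval and not as evidence of similarity.

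The cost is wording. The stated figures become less favourable; enrolment, follow-up and data collection do not change.

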## Discussion

This project will clearly address the relevance, timeliness, and the sustainability of dialysis in the older age group. The provision of dialysis, preferably in a home setting or low level self-care satellite units closer to the individuals’ residences, may allow better integration with primary and community care. If conservative management is shown to be an important and valid option with similar outcomes to dialysis, then this can be appropriately discussed with the individual and their family without this being considered as rationing, or limiting health resources, to this age group (which is often a perception). Elderly patients who do not commence dialysis often survive many months (6), and some may have a better quality of life (HRQoL).

Providing information as to preferred options by this age group related to their expectations and perceived quality of life will immediately influence delivery of healthcare. The data generated by this study will critically inform health care for the older age group.

Results from this study will make possible more informed decision making by future elderly patients and their families as they contemplate renal replacement therapy. Results will also allow health professionals to more accurately describe the impact of dialysis therapy on quality of life and outcomes for patients.

Funding was received from the New Zealand Health Research Council in 2010 (HRC 10/354; NZD$775,000). A publication reporting early data from the first year of the project is currently being prepared for publication.
